### Sample size

The sample size was calculated on the hypothesis that experimental intervention (BCI-MI training) is superior in improving the primary outcome measure. Based on preliminary findings in the Upper Extremity Motor Scores (UEMS) from the International Standards for Neurological Classification of SCI (ISNCSCI) ASIA Impairment Scale (AIS) [35] in experimental vs control condition, alpha level at 0.05, statistical power at 80%, and one-tailed t-test, 15 participants per group (Control-MI and BCI-MI) are needed. The analysis was performed using the statistical software STATISTICA 8.0 (Stat Soft. Inc. 1984–2007, USA) according to the algorithm implemented in the tool Power Analysis/Sample Size Calculation.

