**Fig. 1 Fig1:**
[figure not shown]
DiSCIoser Randomized Controlled Trial summary. All Spinal Cord Injury (SCI) patients admitted to the Spinal Unit at Fondazione Santa Lucia IRCCS will be screened (T enrol) for eligibility according to Inclusion/Exclusion criteria. The evaluation according to the International Standards for Neurological Classification of SCI (ISNCSCI) ASIA Impairment Scale (AIS) and the predicted mean Upper Extremity Motor Score (UEMS) recovery will be used for eligibility. Eligible participants will be presented with the Informed Consent and recruited (30 participants). Clinical, neuropsychological, neurophysiological and neuroimaging assessments will be performed before (T pre) and after (T post) the intervention

The primary outcome is the Graded Redefined Assessment of Strength, Sensibility and Prehension (GRASSP) somatosensory sub-score [32]. Secondary outcomes are the GRASSP motor sub-score, the self-care section of the Spinal Cord Independence Measure (SCIM) [33] scale and a battery of clinical/functional scales (See Table 1 for details) to monitor upper limb muscle strength, tone, pain, and functional ability. Other pre-specified outcome measures are extracted from neuropsychological, neurophysiological and neuroimaging assessment before and after training. The overall outcome assessments are detailed in the Assessment section. The outcome assessors are blinded to the treatments.

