#### Primary

Changes from pre- $$({T}_{pre})$$ to post- $$({T}_{post})$$ treatment in GRASSP somatosensory scores of bilateral arms (12 is the maximum score for each side, equal to physiological condition) [32] are the primary outcome measure of the trial. Those changes will be computed assessing the difference between $${T}_{post}$$ and $${T}_{pre}$$ scores, or by computing the effectiveness, defined as the ratio between $${T}_{post}$$-$${T}_{pre}$$ difference and the maximum possible improvement for that specific scale, expressed in percentage.

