#### Secondary

The secondary outcome measures are the changes from pre- $$({T}_{pre})$$ to post- $$({T}_{post})$$ of the following fields and assessment scales:muscle strength: the GRASSP motor score of bilateral arms that ranges from 0 (maximum impairment) to 50 (normal) for each side [32]; the UEMS and the Lower Limb Motor Score (LEMS) from the ISNCSCI AIS evaluation for the residual strength assessment in upper and lower limb segments, it ranges from 0 to 25 for each arm and leg [35]; the arm will be considered as dominant and non-dominant according to the results of the Edinburgh Handedness Inventory [37];muscle tone: the Modified Ashworth Scale (MAS) for the muscle tone assessment of upper and lower limbs [38] ranging from 0 (absence of augmented muscle tone) to 4 (non-reducible spasticity); the Penn Spasm Frequency Scale (PSFS) for the self-assessment of upper and lower limb spasms frequency (ranging from 0, absence of spasms, to 4, more than 10 spasm each hour) and severity (ranging from 1, mild, to 3, severe) [39];pain: the International SCI Pain Basic Dataset (ISCIBPDS) for pain assessment; a pain-intensity, rating from 0 to 10, quantifies pain impact on activities daily living, humour, and sleep functions [40];functional ability: the GRASSP prehension ability ranging from 0 to 12 for each side and prehension execution ranging from 0 to 20 for each side; the Spinal Cord Injury Independence Measure (SCIM) self-care section score ranges from 0 (maximum impairment) to 20 (independence) [33].

Other specified secondary outcome measures will be extracted from neurophysiological, neuroimaging, neuropsychological and user experience assessments (see below).

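### The 80% power is claimed for the primary GRASSP somatosensory score but was calculated from UEMS, a secondary strength score, so it is unsupported for the primary

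*Protocol article*

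**What the plan says.** All references are to the protocol article. The Sample size section opens with the purpose of the calculation: "The sample size was calculated on the hypothesis that experimental intervention (BCI-MI training) is superior in improving the primary outcome measure". The next sentence names its input: "Based on preliminary findings in the Upper Extremity Motor Scores (UEMS"), comparing experimental with control condition. The settings are "alpha level at 0.05, statistical power at 80%, and one-tailed t-test", and the result is that "15 participants per group (Control-MI and BCI-MI) are needed".

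The section on study design is clear about the endpoint: "The primary outcome is the Graded Redefined Assessment of Strength, Sensibility and Prehension (GRASSP) somatosensory sub-score". The Primary subsection of Assessments defines it as the pre-to-post change in "GRASSP somatosensory scores of bilateral arms (12 is the maximum score for each side, equal to physiological condition"), computed either as a raw difference or as a percentage of the maximum possible improvement. The Primary analyses subsection analyses that same score and specifies two-tailed testing.

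UEMS appears among the secondary outcomes, under muscle strength: "the UEMS and the Lower Limb Motor Score (LEMS) from the ISNCSCI AIS evaluation for the residual strength assessment". Of its scale the article says "it ranges from 0 to 25 for each arm and leg".

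**The concern.** A power figure belongs to one endpoint: it follows from the difference and the SD assumed for that endpoint. Here the claim is attached to a sensory score, while the only named input is a strength score with a different range. Two outcomes can be correlated within patients and still have different standardised treatment effects, and the article does not argue that these two are alike.

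The Inclusion/exclusion criteria add a reason not to assume it. They select on motor deficit, through a predicted UEMS recovery below 40/50, and set no threshold for sensory deficit. Room to improve is therefore addressed for UEMS and left open for the primary.

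At stake is how the result is read. This calculation is the article's only justification for 30 participants. If the primary comparison is not significant, a reader who relies on the Sample size section will take it as the result of a trial with 80% power on that outcome, which the article has not shown.

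**Working it through.** **1. Inputs.** From the article: 15 per group, 1:1 allocation, alpha 0.05, power 80%, one-tailed t-test (Sample size; Study design); two-tailed testing in the analysis (Primary analyses). Not given: a mean difference, SD or standardised effect for GRASSP somatosensory change. The UEMS figures are not printed either, which is ordinary condensation in an article and carries no weight here.

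**2. What the stated n implies.** Without an effect size, n cannot be reproduced forwards, so I solved backwards for the standardised effect d (true difference in mean change divided by SD of change). For two groups of n, the t statistic has 2n − 2 degrees of freedom and noncentrality d × √(n/2). With n = 15 this is 28 degrees of freedom and d × √7.5 = 2.739 d. One-tailed power is the probability that this noncentral t exceeds 1.701.

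- 80% power at n = 15 gives d = 0.931.
- 80% power at n = 14 gives d = 0.965.

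Because n is rounded up, any d from about 0.93 to 0.97 leads to 15 per group. The stated n is therefore internally possible, for a large effect that comes from UEMS.

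**3. What this means for the primary.** The 80% carries over only if the standardised effect on the GRASSP somatosensory score is also about 0.93. That effect is unknown, so the values of d below are assumptions, shown as a range. All figures are for 15 per group.

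| Assumed d for the primary | Power, one-tailed 0.05 (as in Sample size) | Power, two-tailed 0.05 (as in Primary analyses) |
|---|---|---|
| 0.5 | 38% | 26% |
| 0.6 | 48% | 35% |
| 0.7 | 59% | 46% |
| 0.8 | 69% | 56% |
| 0.93 | 80% | 69% |
| 1.0 | 85% | 75% |
| 1.1 | 90% | 83% |

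**4. Separating two causes.** Reading down the one-tailed column shows what the endpoint mismatch alone can do. Reading across a row shows the loss from calculating one-tailed and testing two-tailed, for example 80% to 69% at d = 0.93. That loss would occur even if the UEMS effect applied exactly to the sensory score, and it is a separate defect.

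**5. Detectable difference under the planned test.** Two-tailed, 80% power at 15 per group needs a true d of 1.06. This is not the threshold for significance: an observed difference of about 2.048 × √(2/15) = 0.75 pooled SD already reaches p < 0.05.

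**The case against.** The strongest objection is that nothing in the article shows the sensory effect to be smaller than the UEMS effect. That stands. A reader might infer that the trial is underpowered for its primary outcome and will probably miss a real effect. The article does not support this: with no GRASSP somatosensory effect or SD, true power could be below or above 80%, and the last two rows of the one-tailed column are above it. Nor can one say that a UEMS effect is uninformative about sensibility. What can be said is that no link is stated.

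A ceiling on the primary score does not by itself set it apart, since UEMS is also bounded, at 25 per arm. The article's plan to use a Wilcoxon Mann–Whitney test for discrete measures may apply to a score with a maximum of 12 per side, so the t-test figures are approximations.

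It can also be argued that the correction is text only and that neither the type I error nor the validity of the estimate is affected. This is true and limits the consequences. It does not make the power statement correct, and printing the UEMS figures would not do so either.

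**Conclusion.** The point holds. The article names the variable behind its sample size, and it is not the primary outcome for which the power is claimed. The 80% is unsupported for the GRASSP somatosensory score, and the direction of the error is unknown. For sensory effects of 0.5 to 0.93 SD, power at 15 per group runs from 38% to 80% on the protocol's one-tailed basis, and from 26% to 69% under its planned two-tailed test; only the first range is due to the endpoint mismatch alone. These figures assume a t-test, equal SDs and all 30 participants analysed.

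**What to change.** Restate the Sample size section so that the 80% (one-tailed) refers to UEMS only. For the GRASSP somatosensory change, add one of the following under the planned two-tailed test:

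- power at 15 per group over a range of standardised effects, as in the table; or
- the true difference detectable with 80% power, about 1.06 SD of change (t-test approximation).

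Say which of the two definitions of change in the Primary subsection the SD refers to, raw difference or percentage effectiveness, because they have different SDs. If the SD is taken from pooled blinded data, note that it includes any treatment difference: with equal groups the inflation is about √(1 + d²/4), which at d = 1.06 is √1.281 = 1.13, or 13% too large.

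The cost is a text change and, if chosen, one blinded SD calculation. No participants are added and the planned test is unchanged. The price is a less favourable power statement.

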### Randomization procedure and methods

The random allocation sequence of participants to experimental (BCI-MI training) or control (Control-MI training) intervention groups will be generated by using Matlab (The MathWorks Inc, Natick, Massachusetts, USA, release 2019a).

The randomization sequence will be stratified by age (2 categories: ≤ 50 years old and > 50 years old) [61] and by GRASSP somatosensory scores (2 categories: ≤ 8 and > 8). A 1:1 allocation ratio will be used. For each stratum, the sequence will include 30 random allocations. The allocation sequence is securely stored at FSL. Randomization of participants will stop after randomization of the 30th participant in the study by summing participants in all strata.

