### Statistical analysis

#### Primary analyses

Baseline characteristics will be described by summary statistics for each group (experimental and control intervention). Differences between groups at baseline $${T}_{pre}$$ will be tested to check that the groups do not differ statistically at baseline.

The primary analysis will be performed in per protocol (PP) population on GRASSP somatosensory score changes between $${T}_{pre}$$ and $${T}_{post}$$. The PP will include all randomized participants who will perform (minimum) 12 training sessions. T-test or Wilcoxon Mann–Whitney rank test for independent groups will be used to compare continuous and discrete outcome measures respectively. Statistical significance will be assessed by two-tailed test.

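### The sample size rests on a one-tailed t-test but the primary analysis is two-tailed, so the stated 80% power does not apply to the planned test

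*Protocol article*

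**What the plan says.** All references are to the protocol article.

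- **Sample size:** the number per group is derived from preliminary UEMS findings in the experimental versus the control condition, with "alpha level at 0.05, statistical power at 80%, and one-tailed t-test, 15 participants per group (Control-MI and BCI-MI) are needed". No mean difference, SD or standardised effect is printed.
- **Primary analyses:** "Statistical significance will be assessed by two-tailed test". No significance level is attached to this sentence. The 0.05 in the Sample size section is the only level in the article. The choice of test is given as: "T-test or Wilcoxon Mann–Whitney rank test for independent groups will be used to compare continuous and discrete outcome measures respectively".
- **Primary analyses, population:** the primary analysis is per protocol. "The PP will include all randomized participants who will perform (minimum) 12 training sessions".
- **Randomization procedure and methods:** "Randomization of participants will stop after randomization of the 30th participant in the study by summing participants in all strata". The enrolment total is therefore exactly 2 × 15, the number said to be needed.

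**The concern.** The calculation and the analysis use different tests. At a level of 0.05, a one-tailed test puts all of the error in one direction. A two-tailed test puts 0.025 in each, so its critical value is higher and its power at the same effect is lower. The two statements would agree only if the two-tailed test were run at 0.10, or if the analysis were one-tailed. The article says neither.

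The trial aims to show superiority with 30 participants. A non-significant result would be read as coming from a trial with a 20% chance of missing the planned effect, when that chance is higher under the plan's own assumptions. The mismatch also leaves a result with a one-sided p between 0.025 and 0.05, in favour of BCI-MI, open to two readings: significant by the rule in the Sample size section, not significant by the rule under Primary analyses.

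**Working it through.** **Inputs.** Level 0.05, power 80%, one-tailed t-test and 15 per group (Sample size); 1:1 allocation (Study design); two-tailed test (Primary analyses). The effect size and SD are not given.

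**Method.** For two independent groups of n with standardised difference d, the t statistic has df = 2n − 2 and noncentrality d·√(n/2). Power is the probability that a noncentral t exceeds the critical value (plus the negligible opposite tail when two-tailed).

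**Step 1: the plan's own figure.** Without an effect size, 15 per group cannot be reproduced directly, so it is inverted. Assume that 15 is the smallest n giving at least 80% one-tailed power.
- Lower bound: d at which n = 15 gives exactly 80% one-tailed: d = 0.931. Check: df = 28, critical value 1.701, noncentrality 0.931 × √7.5 = 2.55, power 80.0%.
- Upper bound: d at which n = 14 would already give 80%: d = 0.965. At n = 15 this gives 82.5% one-tailed.

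**Step 2: the same effects under the planned test.** The two-tailed critical value at df = 28 is 2.048 instead of 1.701.

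| d | one-tailed power, n = 15 | two-tailed power, n = 15 | smallest n per group for two-tailed 80% |
|---|---|---|---|
| 0.931 | 80.0% | 69.2% | 20 |
| 0.965 | 82.5% | 72.3% | 18 |

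The shortfall against the stated 80% is 80 − 72.3 = 7.7 to 80 − 69.2 = 10.8 points. As a cross-check, the normal approximation, with its own implied range d = 0.908 to 0.940, gives 70.1% to 73.0%.

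**Step 3: what 15 per group can detect.** Solving for two-tailed 80% power at n = 15 gives d = 1.06. This needs no unseen input beyond applying the 0.05 level to the two-tailed test.

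**Step 4: sensitivity to the assumption in step 1.** If 15 had been rounded up from a smaller minimum, the implied effect would be larger. If 13 per group sufficed one-tailed, d = 1.00 and two-tailed power at 15 is about 76%. If 12 sufficed, d = 1.05 and it is about 79%.

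**Step 5: fewer analysed than randomised (illustration only).** The article gives no expected exclusion rate. With 13 analysed per group, the step 1 effects give 62.4% (d = 0.931) to 65.6% (d = 0.965) two-tailed.

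**The case against.** There are four serious points on the other side.

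1. **The 69% to 72% is back-solved.** It depends on 15 being the unpadded minimum and on the two-tailed test being run at 0.05. This stands as a condition. The wording "15 participants per group (Control-MI and BCI-MI) are needed" supports the minimum reading but does not prove it. Step 4 shows the figure rising to 76% or 79% if the number was padded by two or three per group. The contradiction in sidedness does not depend on any of this.

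2. **It is not the power for the primary outcome.** This also stands. The planning effect is on the UEMS, a motor score, while the primary outcome is the change in the GRASSP somatosensory score. If that score, with a maximum of 12 per side, is treated as discrete, the article assigns it the Mann–Whitney test and a t-test calculation is only approximate. A reader might infer that the trial really has a miss rate of about 30% on its primary outcome. The document does not support that: it gives no effect or SD for this outcome.

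3. **Exclusions may not occur.** A reader might infer that the analysed number must fall below 30. That goes too far. The threshold is 12 of 36 planned sessions, one third of the course, in patients who are already in hospital, so zero exclusions are possible. What stands is that enrolment equals the stated requirement exactly, so any exclusion takes the analysed number below it.

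4. **A two-tailed test is the conservative choice.** True: type I error is not inflated and no positive finding becomes invalid. The harm is confined to the power statement and to the ambiguity over which rule decides significance. A directional hypothesis might justify one tail, but the analysis section chose two.

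**Conclusion.** The point holds in conditional form. The Sample size and Primary analyses sections contradict each other on sidedness, nothing in the article reconciles them, and the stated 80% does not apply to the planned two-tailed test.

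The overstatement is about 8 to 11 percentage points (power of 69% to 72%), provided that 15 is the minimum n for the stated one-tailed calculation and that the two-tailed test uses 0.05. Under the same level, two-tailed 80% power with 15 per group needs a standardised difference of about 1.06. Per-protocol exclusions, if there are any, would reduce power further; the 62% to 66% at 13 per group illustrates this and is not a forecast. True power for the GRASSP somatosensory change cannot be determined from the document.

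**What to change.** Keep the two-tailed test and correct the Sample size section so that it describes that test:

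- Give the two-tailed power at 15 per group, recomputed by the authors from their own effect size and SD, and print those inputs. The result should be about 70% if 15 was the minimum n. That figure should not be copied in without the recalculation.
- State that 80% two-tailed power at 0.05 with 15 per group needs a standardised difference of about 1.06.
- State the 0.05 level beside the two-tailed test under Primary analyses.
- Say that the planning effect is on the UEMS and that power for the GRASSP somatosensory outcome is therefore uncertain, and that the figure assumes all 30 are analysed.

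The cost is one corrected paragraph and one added phrase. Enrolment does not change, but the stated power becomes less favourable. Restoring 80% through numbers would instead take 18 to 20 per group under the same assumptions (36 to 40 in total); this correction does not require it.

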### Inclusion/exclusion criteria

The specific Inclusion and Exclusion criteria are listed below:

Inclusion criteria:age between 18 and 70 years,current hospitalization at FSL site for rehabilitation care,subacute traumatic cervical SCI (30–90 days after the event),classification according to ISNCSCI ASIA Impairment Scale A-D,lesion level between C1 and T1,predicted average UEMS recovery of less than 40/50 [36].

Exclusion criteria:other conditions (present or previous) potentially affecting sensorimotor function of the upper extremities,significant traumatic brain injury,history of epilepsy or previous neurological deficits,psychiatric or cognitive comorbidities involving motor planning problems or impulsivity (unable to follow commands),inability to give informed consent and understand training requirements,concurrent enrolment in other clinical research trials focusing on specific unconventional treatments targeting upper limb function.

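### No entry criterion requires a hand sensory deficit, so participants already at the maximum of the sensory primary outcome on both sides can be randomised and cannot improve

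*Protocol article*

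**What the plan says.** The protocol article's Inclusion/exclusion criteria set one threshold on upper-limb function: "predicted average UEMS recovery of less than 40/50". The other injury-related entries are time since injury, "classification according to ISNCSCI ASIA Impairment Scale A-D" and "lesion level between C1 and T1". The Fig. 1 legend agrees, stating that AIS evaluation and "predicted mean Upper Extremity Motor Score (UEMS) recovery will be used for eligibility". No inclusion or exclusion item refers to hand sensation.

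Under Primary (Outcome assessments), the outcome is the pre-to-post change in "GRASSP somatosensory scores of bilateral arms (12 is the maximum score for each side, equal to physiological condition"). It may be computed as a difference or as a percentage, the percentage being the difference divided by "the maximum possible improvement for that specific scale".

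Randomization procedure and methods stratifies by age and "by GRASSP somatosensory scores (2 categories": at most 8, and above 8). Randomisation stops at the 30th participant counted over all strata, so the share in the upper stratum is not limited. Under Primary analyses, the per-protocol population is defined by a minimum of 12 training sessions, and testing is two-tailed.

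**The concern.** Entry is controlled on a motor measure and the primary outcome is sensory. Under the stated criteria, someone with a low predicted motor score and intact hand sensation is eligible, falls in the upper stratum and stays in the per-protocol set. That person's primary outcome can only be zero or negative in either arm.

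In a trial of 30, each such participant shrinks the mean difference that the primary test has to detect. The sample size does not allow for this, because it was built on preliminary UEMS (motor) data. The percentage form adds a second problem: if its denominator is the room left from the pre-treatment score, a participant at the maximum has a denominator of zero and no defined value.

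**Working it through.** **Can a ceiling participant enter and be analysed?** Each rule was checked for a participant at 12 on both sides.

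- Entry: no criterion caps the sensory score. AIS A–D and level C1–T1 do not require a hand sensory deficit.
- Stratum: above 8, with no upper limit. The article does not say whether the cut-off of 8 is per side (maximum 12) or bilateral (maximum 24), but the upper stratum contains the maximum either way.
- Analysis set: defined by sessions attended only.

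So the answer is yes.

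**The plan's own figure.** Sample size gives 15 per group, alpha 0.05, 80% power and a one-tailed t-test, but no mean difference or SD. The 15 cannot be reproduced forward, so the effect is back-solved. With n = 15 per arm, 28 degrees of freedom and noncentrality d·√(n/2), 80% one-tailed power needs d = 0.931 (0.908 by the normal approximation). The same d gives 69% power under the two-tailed test in Primary analyses.

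**Dilution model.** Inputs that are assumptions, not in the document:

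- c, the share at ceiling, with change fixed at 0
- μ, the mean control-arm change among the others, set to 0, 0.5 or 1.0 SD
- within-arm SD of 1 among the others, with experimental mean μ + 0.931

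Formulas:

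- Contrast = (1 − c) × 0.931
- Variance of an arm with mean m among the others = (1 − c) + c(1 − c)m²
- Standardised effect = contrast / √(average of the two arm variances), entered in the noncentral-t power at 15 per group

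Worked case, c = 0.10 and μ = 1.0:

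- Contrast: 0.9 × 0.931 = 0.838
- Control variance: 0.9 + 0.09 × 1² = 0.990
- Experimental variance: 0.9 + 0.09 × 1.931² = 1.235
- Average variance: 1.113
- Standardised effect: 0.838/√1.113 = 0.79
- Power: 68% one-tailed, 56% two-tailed

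Results over μ = 0 to 1.0 SD:

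| Share at ceiling | One-tailed power | Two-tailed power |
|---|---|---|
| none | 80% | 69% |
| 1 of 30 | 76–78% | 64–67% |
| 2 of 30 | 72–77% | 60–65% |
| 10% (3 of 30) | 68–75% | 56–63% |
| 20% (6 of 30) | 57–69% | 44–56% |
| 30% (9 of 30) | 48–62% | 35–49% |

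The better end of each range is no control change; the worse end is control change of 1 SD. Scaling only the contrast and holding the SD at 1 gives 72%/60%, 63%/50% and 54%/41% at 10%, 20% and 30%, which lies inside these ranges.

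**Where the loss comes from.** Average variance at c = 10%, 20% and 30%:

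- μ = 0: 0.94, 0.87, 0.79
- μ = 0.5: 1.00, 0.98, 0.94
- μ = 1.0: 1.11, 1.18, 1.20

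Variance rises clearly only with large control recovery. Power falls in every case because the contrast shrinks.

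**Percentage form at 12/12 on both sides.** If the denominator is maximum minus pre-treatment score, it is 24 − 24 = 0 and the ratio is undefined. If it is the range of the scale, the ratio is defined.

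**The case against.** The strongest reply is that the size is unknown. The document gives no ceiling share, no sensory effect size and no control-arm change. The 0.93 SD is inferred from a calculation on motor data. A participant counts as being at ceiling only if both sides are at maximum, which may be uncommon in cervical injury, and one or two such participants cost roughly 2 to 8 points of one-tailed power. This stands, and it is why the result is a range that starts at 1 of 30.

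A second reply is that the design does consider baseline sensation. It stratifies on it, and Secondary analyses plans exploratory analyses within the strata. That is fair, but stratification balances ceiling participants between arms without keeping them out, and exploratory subgroup results do not repair the primary test.

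A third is that broad entry is a legitimate choice in a single-centre trial with motor, prehension and self-care secondary outcomes. It is, and it is a reason to settle the analysis first and treat the entry check as an addition.

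A reader might infer more than the text supports:

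- That eligibility is motor only. AIS grade and lesion level are also criteria; they simply do not require a hand sensory deficit.
- That ceiling participants generally raise the variance. The figures above show otherwise for control change of 0, and for 0.5 SD with 20–30% at ceiling.
- That they carry no information at all. Their score can still fall.
- That the percentage is certainly undefined for them. This depends on how the denominator is read.

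**Conclusion.** The point holds in limited form. The stated criteria admit participants who cannot improve on the primary outcome, and no later rule removes them or allows for them. The mismatch can be read directly from the article, because eligibility and primary outcome are both fixed there.

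The power cost is conditional on an unreported ceiling share, a back-solved 0.93 SD effect and control change between 0 and 1 SD. It is small with one participant at ceiling and serious if the share reaches 20–30%, but the document gives no basis for expecting such a share. The undefined percentage is a problem only under the room-left reading. The change is worth making because it is cheap, not because a large loss has been shown.

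**What to change.** 1. **Outcome and analysis.** Define the primary outcome as the absolute bilateral change in GRASSP somatosensory score, analyse it with adjustment for the pre-treatment score, and drop the percentage alternative from the primary analysis. Every participant assessed at both times then has a defined value. This costs a line of text and no new data. It does not restore the diluted contrast.

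2. **Entry check, in addition.** At the pre-treatment assessment, before randomisation, confirm that the bilateral GRASSP somatosensory score is below its maximum. The score is already needed then for stratification, so no new assessment is required. The cost is an amendment, slightly slower recruitment, a few exclusions after consent (the score is taken after initial screening) and the loss of secondary-outcome data from those patients. It removes full-ceiling participants only. Someone with one or two points of room would still enter, so near-ceiling dilution remains.
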